**Methods:**

This multicenter, open-label, large-sample, randomized controlled trial was performed in China and included 500 children with HSPN exhibiting mild pathological patterns. The treatment group to control group ratio was 2:1, and each group was further stratified into two types, light and heavy, according to urinary protein quantification and pathological type. The treatment group received tripterygium glycosides (TGs), tanshinone IIa sodium sulfonate injection, and Chinese herbs selected based on syndrome differentiation in TCM. The heavy and light subgroups received treatment courses and dosages of TG. In the control groups, the light group received benazepril hydrochloride tablets, low molecular weight heparin calcium injection, dipyridamole tablets, and a Chinese medicine placebo, while the heavy group received the same treatment plus prednisone. All groups were treated for 3 months and then followed up for 9 months. The efficacy and safety of the treatments were then evaluated among the groups.

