### Intervention

The participants will be divided into two groups: an experimental group treated with TCM and a control group receiving regular treatment. In each arm, light type and heavy type HSPN will be reclassified based on the level of proteinuria and biopsy results. Eligible patients will be treated and observed for a total of 48 weeks. The first 12 weeks comprise the drug therapy stage, and the next 36 weeks comprise a follow-up observation stage.
Treatment stage (0–12 weeks).
TCM group.

TG: for light type HSPN, the initial dosage is 1.5 mg/kg/day (maximum of 90 mg) for the first 4 weeks. For heavy type HSPN, the initial dosage is 2 mg/kg/day for the first 2 weeks and is reduced to 1.5 mg/kg/day (maximum of 90 mg) for the following 2 weeks. Both groups will continue to receive treatment for another 8 weeks at a dosage of 1 mg/kg/day taken orally 2–3 times per day for a total of 12 weeks.

Tanshinone IIa sodium sulfonate injection (TIIa): an intravenous drip of TIIa administered at a dosage of 1 mg/kg/day (maximum of 50 mg) in combination with 100–250 ml of a 5% glucose solution (GS) for 2 weeks.

TCM based on syndrome differentiation: in TCM-treated patients, Chinese herbs will be administered as Qingrezhixue granules according to syndrome differentiation for 12 weeks. The specific TCM treatments are presented in Table 2.
b)Regular group.

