GC: for severe type HSPN, prednisone will be given orally at 1.0 mg/kg/day for 12 weeks. In the first 4 weeks, GC is given at 1.0 mg/kg/day (maximum dose should not exceed 30 mg). The initial dose (1.0 mg/kg/day) should be reduced by 5 mg every other day for 4–8 weeks, and the dose should be reduced by 5–10 mg every week for 8–12 weeks. GC is not necessary and will not be administered for light type HSPN.LMWHC injection: both types will be given LMWHC via a subcutaneous injection at 100u/kg/d once a day for the first 2 weeks.Benazepril hydrochloride tablets (Lotensin): both types will be given Lotensin at 5–10 mg/day orally once per day for 12 weeks.Dipyridamole tablets (Persantine): both types will be given Persantine at 3 mg/kg orally three times per day for 12 weeks.Chinese medicine placebo: to increase compliance by patients seeking TCM treatment in Chinese hospitals, one kind of granule placebo similar to Qingrezhixue granules will be used in the control group, and there is no additional placebo used to blind for the other components of the TCM intervention (TG tablets and tanshinone IIa injections).Changes in proteinuria and hematuria and liver and kidney function will be monitored during treatment, as shown in Table 3.

**Table 2 Tab2:** Herb addition based on traditional Chinese medicine syndrome differentiation

Yin deficiency complicated with blood stasis Add Chinese herbs as Qingrezhixue granules: *Rhizoma anemarrhenae*, *Cortex phellodendri*, *Rhizoma polygonati*	
Main symptoms of yin deficiency	Red tongue with less or no moss and a dark red throat, a low-grade fever with night sweat, sparse purpura
Secondary symptoms of yin deficiency	Feverishness in the palms and soles, dry mouth with thirst, a weak and rapid pulse
Symptoms of blood stasis	Dark purple tongue or bruises on tongue body; varicose veins or blood stasis in sublingual veins; fixed pain or intense pain causing an aversion to touch; thrombogenesis; dark or blue color (cyanosis) in the face, mouth, or gums, around the eyes, or in the lips and extremities; sluggish or intermittent pulse; hematuresis, epistaxis, ecchymosis, or tarry stool; dark and dull complexion; laboratory examination indicating blood circulation stasis
Diagnostic criteria	2 main symptoms of yin deficiency (or 1 main + 2 secondary symptoms) + 1 main symptom of blood stasis
Blood heat complicated with blood stasis Add Chinese herbs as Qingrezhixue granules: ComuBuball, Radix arnebiae seu lithospermi	

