Blood system: the white blood cell count (WBC) and platelet count (PLT).In patients taking immunosuppressors or prednisone, there is a potential risk of abnormalities in the blood system in terms of leukocyte and platelet counts. Blood tests were performed to determine the leukocyte count 17 times during and after treatment, as already described.Liver and kidney function test: glutamate alanine transferase (ALT), glutamate aspartate transferase (AST), serum creatinine (Scr), and blood urea nitrogen (BUN) levels should be monitored.In patients using any drug, there is a potential risk of dysfunction in the liver and kidney. Because they are the main indicators used to evaluate liver and kidney function damage, blood should be drawn from the vein to perform ALT/AST and Scr/BUN tests 11 times during and after treatment.

Time frame for testing: week 0 (before treatment)/week 1/week 2/week 4/week 8/week 12 of the treatment phase and week 20/week 28/week 36/week 44/week 48 of the follow-up phase.

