### Randomization

Participants will be randomized at a 2:1 ratio by the Central Randomization System of the China Academy of Chinese Medical Science, which is an online, central randomized service. Allocation concealment will be ensured, as the service will not release the randomization code until the patient has been recruited into the trial, which takes place after all baseline measurements have been completed.

The study participants are stratified by disease subtype. Both heavy type and light type will be included in each subcenter. The trained clinicians divide those children with HSPN who met the requirements into light type and heavy type according to the amount of urine protein within 24 h. After signing the informed consent, clinicians will log into the central random system according to their account password, and then click “random” under the corresponding subtype to conduct random grouping.

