### Statistical analysis

All statistical analyses in the study will be carried out by a third party, the Chinese Academy of Traditional Chinese Medicine, using SAS version 6.12, which is validated software for clinical studies. Logistic regression is used to show a difference in the prevalence of clinical control/remission in both groups, including age, gender, place of residence, parents’ educational background, and so on. For the outcome “time from positive to negative for urinary protein and urinary occult blood”, a Cox proportional hazards model is used. The incidence is described for adverse events and Fisher’s test will be used for comparison. Besides, groups and time of therapy on curative effect will be considered. If there are interaction effects between groups, simple effect analysis is performed; if not, grouping effect/time of therapy on curative effect should be considered separately.

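### Fisher's test for adverse events is named without regard to disease type, although the control regimen differs between light and heavy type and one combined comparison could dilute or mask a type-specific harm

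*Protocol article*

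**What the plan says.** The whole plan for comparing adverse events is the sentence "The incidence is described for adverse events and Fisher’s test will be used for comparison" in the Statistical analysis section. It does not say which groups form the table, how many tests there are, or whether type enters. The interaction and simple-effect language later in that section concerns curative effect, not safety. The abstract adds only this: "The efficacy and safety of the treatments were then evaluated among the groups".

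The design separates the types. Under Randomization: "The study participants are stratified by disease subtype". Under Intervention, the regular arm differs by type. For light type, "GC is not necessary and will not be administered for light type HSPN"; for the heavier type, "for severe type HSPN, prednisone will be given orally at 1.0 mg/kg/day for 12 weeks". The starting dose of tripterygium glycosides (TG) also differs: "for light type HSPN, the initial dosage is 1.5 mg/kg/day (maximum of 90 mg) for the first 4 weeks" against "For heavy type HSPN, the initial dosage is 2 mg/kg/day for the first 2 weeks". From week 3 the two types have the same TG dose per kg. The Outcomes section itself recognises that in patients "taking immunosuppressors or prednisone, there is a potential risk of abnormalities in the blood system".

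**The concern.** On the article's own account, TG (as an immunosuppressant) and prednisone are both possible sources of blood abnormalities. In light type only the TCM arm receives one of them. In heavy type both arms do: TG on one side, prednisone on the other. The light-type comparison therefore asks what the TCM programme adds over a steroid-free regimen, and the heavy-type comparison asks how it compares with a steroid-containing one.

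A single two-by-two table of TCM against regular treatment mixes these questions. An excess of events on TCM in the 380 light-type children could be diluted by heavy-type children in whom both arms have similar rates, or offset by steroid events among heavy-type controls. A reader could then take an unremarkable overall result as reassurance for light type when the data do not support it. For a paediatric trial that sets out to assess the safety of a programme graded by type, that is a material risk of misreading.

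**Working it through.** **Inputs from the article.** 380 light and 120 heavy patients (Sample size calculation) and 2:1 allocation (Randomization). This gives about 253:127 in light type, 80:40 in heavy type and 333:167 combined. The article states no figure for the adverse event comparison, so there is none to reproduce; its sample size of 405 before inflation concerns efficacy.

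**Weights.** Allocation is 2:1 in both types, so the combined risk difference is close to

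D = (380/500) × D_light + (120/500) × D_heavy = 0.76 × D_light + 0.24 × D_heavy.

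Exact cancellation needs D_heavy = −(380/120) × D_light = −3.17 × D_light. A 10-point excess in light type is cancelled only by a 31.7-point difference the other way in heavy type. Partial masking needs less:

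- D_light = +10 and D_heavy = −20: 0.76 × 10 − 0.24 × 20 = 7.6 − 4.8 = 2.8 points.
- D_light = +10 and D_heavy = 0: 7.6 points.

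**Power.** All event rates below are assumptions. Each entry is the probability that a two-sided Fisher test gives p < 0.05, summed over all binomial outcomes at the sample sizes above. Independent simulations agree to within about 2 percentage points.

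| Light, TCM v control | Heavy, TCM v control | Combined rates | Combined test | Within light | Within heavy |
|---|---|---|---|---|---|
| 20% v 10% | 20% v 40% | 20.0% v 17.2% | 9% | 70% | 60% |
| 20% v 10% | 20% v 50% | 20.0% v 19.6% | 3% | 70% | 90% |
| 20% v 10% | 25% v 25% | 21.2% v 13.6% | 53% | 70% | 4% |
| 20% v 10% | 20% v 10% | 20.0% v 10.0% | 82% | 70% | 23% |
| 20% v 10% | 30% v 15% | 22.4% v 11.2% | 88% | 70% | 40% |
| 10% v 10% | 30% v 30% | 14.8% v 14.8% | 4% | 4% | 4% |

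The first two rows show masking, the third dilution, the next two a gain from combining, and the last that the combined test keeps its level when treatment has no effect in either type.

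**Does stratifying alone help?** No. In simulation a Mantel-Haenszel test rejected about 10% of the time in the first row and 4.4% in the second. A stratified average of opposite effects is still an average; only results shown by type reveal the conflict.

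**Homogeneity check.** A z test on the difference of log odds ratios (Woolf variance, 0.5 added to each cell) detects the conflict in the first row about 92% of the time, but the milder difference in the third row only about 31% of the time. A non-significant homogeneity test is therefore weak evidence of agreement, and the two estimates must be read with their intervals.

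**Precision by type.** The approximate half-width is 1.96 × √(p₁(1−p₁)/n₁ + p₂(1−p₂)/n₂). For heavy type at 20% v 40%: 1.96 × √(0.16/80 + 0.24/40) = 17.5 points. For light type at 20% v 10%: 1.96 × √(0.16/253 + 0.09/127) = 7.2 points.

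**The case against.** A reader might infer that the plan prescribes one pooled, unstratified test. The article does not say so: neither the number of tests nor the grouping is stated, and Fisher's test within each type would satisfy the sentence. The Background describes two groups with two subgroups each, and the abstract's wording on safety is equally open. Whether tables are split by type may be settled in an analysis plan that is not shown. That much stands, and the point is therefore conditional on how the sentence is carried out.

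A reader might also infer that a combined test is biased, or that it would give a wrong safety conclusion for both types. The documents support neither. Allocation is 2:1 in each type, so type does not confound the comparison. Full cancellation needs an opposite heavy-type difference more than three times the light-type one, and no event rates are given to make that likely. If the types go the same way, combining gains power. The overall comparison also answers a fair programme-level question, and safety does not rest on one p-value: incidence is described, and blood counts and liver and kidney function are monitored separately.

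The TG dose contrast is also limited, since it is confined to the first 2 weeks. Prednisone is the main difference.

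What the objection does not remove is that the only named safety test takes no account of a factor that stratifies randomisation and changes the comparator, and that the section's only interaction language is about efficacy.

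**Conclusion.** The point holds as a gap in how the safety comparison is fixed, not as an error in a stated test. Fisher's test is named without regard to type in a design where type determines whether controls receive prednisone. If it is run as a single comparison, the result is a 76:24 average of two different contrasts. Under the assumed light-type rates of 20% v 10%, power falls from about 70% within light type to about 53% when heavy-type rates are equal at 25%, and to about 9% when heavy type is 20% v 40%; it rises to about 82% when the types agree at 20% v 10%. These figures rest on the planned stratum sizes and on invented event rates, so they show what can happen, not what is likely. Reporting by type is worth doing because the within-type comparisons are randomised and nearly free.

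**What to change.** State in the Statistical analysis section that:

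- the overall TCM-versus-regular comparison of adverse events is kept and is stratified by type (Mantel-Haenszel or exact);
- within light type and within heavy type, adverse event incidence by arm, the risk difference with 95% CI and Fisher's test are reported;
- a homogeneity check is given, and the overall result is read as applying to both types only if the two estimates agree, judged by their intervals as well as by the test.

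The trial is reported to be in its statistical stage, so the wording should be settled before comparative adverse event results are looked at. If they have already been seen, the by-type results should be labelled as added later.

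The cost is a few more tables; type is already recorded at randomisation, so no new data are needed. The downsides are extra comparisons, which should be read as safety description rather than as confirmatory tests, and a wide interval in heavy type (80:40).

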### Quality control and quality assurance

It is necessary to take appropriate measures to minimize bias because confounding bias is a key factor that can affect the quality of the test.

We will try to select research centers in different regions and strictly follow the inclusion and exclusion criteria to reduce selection bias. Conduct unified training and assessments of participating researchers and strictly normative data will be performed to reduce measurement bias. To ensure the traceability of laboratory test results and minimize measurement bias, the normal reference values of the laboratory index of each subcenter will be attached.

Concomitant medications should be reduced as much as possible during study implementation.

In addition, the advantages and characteristics of the study will be explained to the subjects in detail before enrollment so that the patients and/or their guardians will fully understand the possible benefits, to improve compliance and to reduce shedding.

It is necessary to establish a three-grade quality control mechanism as the quality supervision organization: researchers conduct self-examination about the cases they have included, inspectors from each subcenter supervise every 4 months, and inspectors from the research group supervise each year. There will be no additional sponsorship.

A comprehensive Data and Safety Monitoring Board will be established to ensure the quality of each step during the testing process as much as possible. As an independent party, the Data Monitoring Committee (DMC) is responsible for the quality control and safety supervision of this study to ensure the safety of the subjects and the validity of the data. By reviewing the implementation, data quality, and evidence of adverse events, the trials can be terminated if the examination indicates that the cases are useless or invalid. When adverse events occur, the main investigator of each center can decide whether to suspend the observation of this case according to the patient’s condition. In addition, the DMC has the right to terminate the trial when data are found to be invalid or useless. The Spirit checklist was shown in Additional file 1.

## Discussion

According to a national cross-sectional survey on the spectrum of biopsy-proven glomerular diseases among children that was performed in China from 2004 to 2014, HSPN (13%) and lupus nephritis (9%) are the most common secondary glomerular diseases in children, and purpura nephritis (23%) is the most common pathological pattern observed in younger children (0–12 years old) [20]. It has been reported that 6–24 per 100,000 children younger than 17 years of age will develop HSP, and approximately 30–50% of patients with HSP will develop HSPN [21]. Most of these patients manifest mainly with microscopic hematuria or proteinuria, while a few exhibit macroscopic hematuria.

Because the treatment strategy for purpura nephritis that is recommended in the current guidelines is insufficient, especially in pathological types without crescents, we propose a comprehensive treatment program in which the TCM TG is used as the main drug in combination with tanshinone, an anticoagulant drug. Furthermore, in this program, TCM is based on syndrome differentiation to evaluate treatment efficacy and provide an evidence base for the treatment of purpura nephritis. The results of this study, which will include a large sample population, will provide a new option for treating HSPN via an integrated treatment program that includes TCM.

### Trial status

Patient recruitment began in 2014 and the trial was re-registered on July 19, 2018 at ClinicalTrials.gov. The programmed completion date for the recruitment was December 31, 2018. The trial is now in the statistical stage of data.

## Data Availability

The data are currently unavailable.

## Abbreviations

ACEI: Angiotensin-converting enzyme inhibitor
ARB: Angiotensin receptor blocker
CRF: Case report form
GC: Glucocorticoid
HSPN: Henoch-Schönlein purpura nephritis
ISKDC: International Study of Kidney Disease in Children
KDIGO: Kidney Disease Improving Global Outcomes
LMWHC: Low molecular weight heparin calcium
NS: Nephrotic syndrome
RPGN: Rapidly progressive glomerulonephritis
TCM: Traditional Chinese medicine
TG: Tripterygium glycoside
